### 2.3. Interventions

#### 2.3.1. Interactive Web-Based Health Program

The intervention group for both clinical trials (F_clin_, W_clin_) will receive the TK-HC. This multimodal health program comprises different coaching modules to enable personalized health coaching according to the chosen health goal and personal health profile. With an evidence-based foundation, it attempts to meet the requirements of quality-assured prevention programs while providing a high degree of usability through interactive, self-directed, and flexible handling [70]. For the present evaluation of the TK-HC, however, the focus will be on individual coaching modules so that the intervention group of the fitness trial (F_clin_) will receive the “TK-FitnessCoaching” (TK-FC) and the intervention group of the weight loss trial (W_clin_) will get the “TK-WeightLossCoaching” (TK-WC). Both coaching modules are intended to achieve sustainable health effects within a 12-week intervention phase to prevent NCDs in the long term. The TK-FC is specialized in promoting physical activity and physical fitness based on endurance, strength, flexibility, and coordination training. The focus of the TK-WC is to assist users in losing and maintaining weight by following the energy density concept and a balanced, healthy diet.

The TK-HC is structured in the same way for both modules. Before starting the program, the user is guided through a multistep anamnesis to check suitability for the chosen health goal and set up an individually tailored program according to the personal health profile. The TK-WC user selects the preferred weight loss goal (3 or 5 kg). After completing the anamnesis, the user is directed to the program platform, consisting of three main areas. The first area (“My health program”) presents a personal dashboard that forms the central part of the program and accompanies the user in everyday life (Figure 1a,b). Here, the user can view an individual weekly plan of daily activities and an overall 12-week coaching plan based on three phases (phase 1: getting to know and trying out (week 1–3), phase 2: consolidating new behaviors (week 4–6), phase 3: anchoring habits (week 7–12)). The user can flexibly adapt these plans to individual needs by selecting activities from 13 fitness (TK-FC) (Figure 2a) and 12 weight loss (TK-WC) (Figure 2b) activities.

The fitness activities focus strongly on endurance training (e.g., “I improve my endurance by running”) and strength training (e.g., “I strengthen my muscles according to a recommended training plan”) as well as on flexibility and coordination training (e.g., “I train my flexibility”) and other health-related fitness courses (e.g., “I train yoga according to instructions”, “I train my back”). All training sessions follow the principle “train—log—analyze” and include detailed training introductions and instructions. Depending on the activity, the sessions can be done at home, in the gym, or outdoors. For endurance and strength activities, a standardized fitness test must be completed to classify the training level and thus select an adequate training plan. After six and eleven weeks, it is recommended to repeat this fitness test to measure the training success objectively. Besides all these activities, additional sports activities can be logged.

The weight loss activities concentrate on tasks that support the user in implementing the energy density concept (e.g., “I achieve a green energy density”) and the principles of a balanced, healthy diet (e.g., “I eat fruit two times and vegetables three times a day”). The key activity of the weight loss program is the nutritional protocol, which is automatically scheduled daily into the coaching plan. This tool supports adherence to the energy density concept and orientation on energy balance by displaying energy density, calorie intake, calorie consumption by physical activity, and fluid intake. In addition, this activity includes a daily macronutrient analysis and a cookbook with many healthy recipes. Another pre-planned activity is to log body weight and waist circumference every week.

All fitness and weight loss activities must be logged daily or weekly and can be modified at any time. The TK-FC user can also select weight loss activities, and the TK-WC user can also choose fitness activities. Both users can further link an activity tracker to the program by transferring the daily step count. Overall, the dashboard visualizes daily planned and logged activities, total activities completed per week, current health goal achievement via widgets, notifications to communicate with the user, personalized daily tips, and a support option. The TK-FC also includes a weekly barrier management tool.

In the second area of the program (“Knowledge”), the user receives evidence-based background information on the respective health goal through a coaching-accompanying knowledge course (“Optimal training” (TK-FC), “Weight loss with energy density concept” (TK-WC)), which is pre-set as a weekly activity in the coaching plan. Moreover, the user can pass other health-related knowledge courses. All courses are split into small articles and are structured interactively using texts, videos, tools, and tests.

Finally, the third area (“My data”) provides an individual analysis profile with visualized data from logged activities as well as the personal health profile and personal data. Furthermore, the user can download the study information and consent form for both the online and the clinical trial and has the option to withdraw participation from the trials and the health program. After program completion, the user gets a coaching summary, and the user can repeat the coaching as often as desired until the end of the study period.

#### 2.3.2. Non-Interactive Web-Based Health Program

The program for the control group for both clinical trials (F_clin_, W_clin_) will consist of a simply designed online platform that offers support in increasing physical activity and physical fitness (F_clin_) or losing and maintaining weight (W_clin_) over a 12-week intervention phase. In terms of content, it consists of a health-related knowledge transfer. Thus, only scientific background information on the respective health goal can be found, structured in short articles, but without interactive components. In addition, the user has access to personal data and the study information and consent form for the online and the clinical trial and has the option to withdraw participation from the trials and the health program.

The study participants of the clinical trials (F_clin_, W_clin_) will receive the respective health program after successful baseline assessment. They will log into the program via the project’s landing page. Criteria for discontinuing, interrupting, or modifying the allocated intervention are defined as feeling unwell, worsening health status, illnesses, diseases, injuries, harms, adverse events, or withdrawal from participation. These criteria will be determined by the study participant or the principal medical investigator of the study. Apart from the interventions, the participant will not be allowed to participate in other studies on physical activity or dietary behavior. For successful study participation and to promote adherence, the study participants will get free medical examinations and an activity tracker (Fitbit Charge 3^TM^) [74]. For participating in the online trial, they will obtain a shopping voucher and discount coupons. Apart from that, all study participants will be given free access to the current version of the TK-HC, including all coaching modules after study completion. As the TK-HC was frozen as a study version before the study started, the current version of the TK-HC contains some new content or features as it is continuously developed [71]. To maintain adherence during the study course, the study participants of the clinical trials will be reminded of the medical examinations by telephone and e-mail. To further monitor adherence, usage behavior data on the health programs will be analyzed within the formative evaluation of the online trials [71].

### 2.4. Outcomes

#### 2.4.1. Primary Outcomes

The primary outcomes aim to measure the achievement of the respective health goal. Therefore, the primary outcome of the fitness trial (F_clin_) is determined as physical fitness, especially cardiorespiratory fitness, measured by maximum oxygen uptake (VO_2_max) (ml/min/kg). Therefore, the study participants will complete the Cooper 12-min run test [75] on a 400 m running track. From the maximum distance covered in meters, the VO_2_max will be estimated using the formula “VO_2_max (ml/min/kg) = (distance in m − 504.9)/44.73” [76]. The test will be performed according to a modified standardized test protocol [77]. The heart rate (220 − age ± 10 bpm) and the Borg ratings of the perceived exertion (RPE) scale (≥17) [78] will be used as subjective and objective exertion criteria and assessed before, during, and after the test. The air temperature, humidity and pressure, and weather conditions will be documented. The study participants will complete a standardized 5-min warm-up and a 10-min cool-down program. Moreover, they will receive a standardized test meal [79]. In case of no exertion or stopping the test due to health problems, the study participants will have to repeat the test.

For the weight loss trial (W_clin_), body weight (kg) is defined as the primary outcome. It will be recorded in a standardized position in underwear and without any accessories (glasses, jewelry, watch) on a bioelectrical impedance analysis scale (seca mBCA 515) [80]. The study participants will be asked to use the toilet beforehand to empty their bladder.

#### 2.4.2. Secondary Outcomes

Various outcomes are set as secondary outcomes. First, for the fitness trial (F_clin_), a further criterion of physical fitness, especially musculoskeletal fitness, is maximum isometric strength (N, kg, lbs). It will be measured with an isometric leg press test using the ProFit Cube software [81] and a handgrip test using a Jamar hand dynamometer [82]. The measurements will be modified to standardized test protocols [83,84,85,86]. A standardized 5-min warm-up phase will precede both procedures. Concerning the first procedure, the study participants will take an individually standardized lying position in an isometric leg press [87] (backrest angle: 10°, slide position: individual, foot position (shoes off): 2, heel position: individual, shoulder fixation: resting against shoulders, arm position: crossed on chest, knee angle: 90°). After a submaximal familiarization phase (4 repetitions, 50–60% of maximum voluntary contraction (MVC): 2–3 s, rest: 1 min), the maximum strength (N) will be recorded bilaterally in three successful trials (3 repetitions, 100% MVC: 2–3 s, rest: 3 min). In the second procedure, the study participants will adopt a standardized sitting (sitting upright, upper arm: adducted to the body, elbow: 90° flexion, forearm: neutral position, wrist: 0–30° extension, ulnar deviation: 0–15°, other arm: relaxed next to the body) and grip position (second handle position). The maximum strength (kg, lbs) will be recorded in three successful trials, alternately left- and right-handed, by squeezing the handle of the hand dynamometer maximally for 2–3 s. The test will be started with the dominant hand. Jewelry and watches will be removed before the test. The maximum and mean value of three successful trials will be documented in both procedures. Verbal encouragement will be given in each trial.

Furthermore, secondary behavioral outcomes are defined for both clinical trials. Physical activity behavior will be measured in terms of steps taken (steps/day), sedentary behavior (minutes/day), and light, moderate, and vigorous intensity physical activity (minutes/week) using the activity tracker Fitbit Charge 3^TM^ [74,88,89,90] and the long version of the International Physical Activity Questionnaire (IPAQ-L) [91,92]. The activity tracker will be given to the study participants at the first medical examination. Data will be collected daily between the first two measurement time points (t0–t1) and seven days after the follow-up measurement time points (t2, t3), respectively, via a personalized study account. Dietary behavior will be assessed by energy and nutrient intake (kcal, µg, mg, g, %) and food consumption (Healthy Eating Index of the German National Nutrition Survey (HEI-NVS)) (g, ml, score) [93,94]. For the weight loss trial (W_clin_), energy density (kcal/g) will additionally be taken to check adherence to the energy density concept [95,96]. All outcomes will be analyzed based on nutritional protocols using the NutriGuide^® Plus^ software (Version 4.8) [97]. The nutritional protocols will be completed seven days after the first medical examination and seven days before the second, third, and fourth medical examination. The study participants will be introduced to the activity tracker and the nutritional protocol at the first medical examination.

Finally, secondary physiological outcomes are set for both clinical trials. Anthropometric outcomes include body weight (kg), body height (cm), BMI (kg/m^2^), fat mass and fat-free mass (kg, %), and waist circumference (cm). For the weight loss trial (W_clin_), however, body weight is considered the primary outcome. The above-mentioned outcomes will be assessed in a standardized position using a stadiometer (seca 274) [98] and a bioelectrical impedance analysis scale (seca mBCA 515) [80,99,100,101]. The waist circumference will be measured with a measuring tape (seca 201) [102] according to a standardized protocol at the midpoint between the lowest rib and the iliac crest. The study participants will be asked to keep their arms loosely at the sides of the body and place their feet together. The investigator will stand on the right side of the subjects. The measuring tape will be used parallel to the floor and lie flat on bare skin without pressing in. The measurement will be taken at the end of a normal expiration. The mean value of two successful measurements (difference: ≤1 cm) will be scored [103]. The study participants will be requested to use the toilet beforehand to empty their bladder, undress except for underwear, and remove jewelry, glasses, watches, and other accessories.

Moreover, systolic and diastolic blood pressure (mmHg) and heart rate (bpm) will be collected via a clinically validated and calibrated electronic blood pressure device [104]. The measurement will be taken on the left upper arm in a standardized way [105,106]. The study participants will be seated upright on a chair (back: supported, legs: uncrossed, feet: flat on the floor, left arm: supported and supinated, free of clothing, jewelry, and watch, right arm: relaxed on the thigh). The cuff will be applied at the right atrium level on bare skin using a correct cuff size (upper arm at least 80% enclosed). After a 5-min rest period, two measurements will be recorded at an interval of 1–2 min. The mean value of two successful readings (systolic blood pressure difference: ≤10 mmHg) will be taken for each parameter. Before and during the measurement, the study participants will be instructed to relax, not to move or talk. The measurement will be carried out in a closed and quiet room without background noise.

Further physiological outcomes are determined as blood levels, especially blood lipids (total cholesterol, low-density lipoprotein (LDL) cholesterol, high-density lipoprotein (HDL) cholesterol, triglycerides (mg/dl)) and blood glucose (fasting plasma glucose (mg/dl), glycosylated hemoglobin (HbA1c) (mmol/mol Hb, %)) taken by blood samples. The samples will be analyzed by the Medical Care Center (MVZ) Clotten in Freiburg.

Finally, vascular health will be examined by endothelial function as flow-mediated dilatation (FMD) (%) via the non-invasive AngioDefender™ system [107]. The assessment will be conducted on the left upper arm in a standardized procedure. The study participants will take the same sitting and arm position as for the blood pressure measurement. A correct cuff size will also be used, and the cuff will be applied on the upper arm at heart level accordingly. After a 10-min rest period, the test will take 8 min. Before starting the test, absolute and relative contraindications will be clarified. In case of pain, discomfort, or complications, the test will be stopped immediately. Before and during the test performance, the study participants will be instructed to relax, not to move or talk. The measurement will be performed in a closed, quiet, and temperature-controlled room (ideally 22–23° C) without background noise. With the FMD and other assessed lifestyle-related health outcomes, the vascular age (days) of the study participants will be calculated by using the Vascular Age Calculator (VAC) [108].

All primary and secondary outcomes will be assessed at four measurement time points (t0: 0 weeks, t1: 12 weeks, t2: 6 months after t1, t3: 12 months after t1), each taking about 4–5 h (F_clin_), and 2–3 h (W_clin_), at the DoSS. All medical examinations will be carried out at the same time of day using standardized procedures by trained and qualified sports and nutritional science and medical staff in separated rooms to protect privacy. The study participants will fast (meal and drinks, nicotine consumption: ≥12 h, alcohol consumption and exercise: ≥48 h). In addition, they will have to sleep sufficiently the night before and will have to be in a current state of good health. These criteria will be checked individually via an anamnesis at the beginning of each medical examination, in which current sensitivities, general habits and disorders of sensitivities, and medication, illnesses, and diseases will also be assessed. Moreover, in case of health problems or diseases, the medical certificate from a general practitioner attesting to the ability to participate in the trial and the health program will be checked, and adverse events will be documented. If these examination conditions are not met, or the examination cannot be performed as scheduled for other reasons, such as coronavirus infection, the examination will be rescheduled as soon as possible, depending on the individual’s state of health. Any rescheduled appointments will be carefully documented for consideration in the data analysis. Furthermore, at the beginning of each measurement, there will be a detailed introduction, instruction, and demonstration of the respective measurement procedure. In case of pain, discomfort, or complications, the measurement will be stopped immediately and, if necessary, repeated. An overview of all primary and secondary outcomes can be found in Table 1.

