From recruitment to successful study enrolment, subjects will have to pass through a multistep process (Figure 3a). If subjects become aware of the study, they will be guided to the project’s landing page, first selecting their personal health goal. Afterwards, they will receive the study information for the respective online trial (F_online_, W_online_), provide written consent, and thus successfully register for the online trial. The study participants will then obtain the first online questionnaire by e-mail. After completing the questionnaire, the study participants from the postcode area 79 will be invited for the respective clinical trial (F_clin,_ W_clin_). To register for the clinical trial, they will have to agree to the study information (Supplementary Materials Files S1 and S2) by their written consent form (Supplementary Materials Files S3 and S4) and enter their contact details and time of availability. After successful registration, they will be randomized in the clinical trial. Within a few days, the study staff will contact the study participants by telephone or e-mail to provide more detailed study information, conduct a complete screening according to the inclusion and exclusion criteria, and make an appointment for the first medical examination. If the criteria are not met, the subjects will not be admitted to the medical examination. Still, they will remain randomized within the clinical trial and participate in the online trial. Within the first on-site medical examination, the eligibility criteria will be rechecked, and any outstanding questions will be answered. After a 7-day follow-up measurement of physical activity and dietary behavior, the baseline assessment and thus the study enrolment will be completed.

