### 5.2. Harms

No particular risks are expected in the context of the clinical trials (F_clin_, W_clin_). In rare cases, skin irritation or infection of the puncture site can occur after blood uptake. Furthermore, muscle soreness can occur in the following days after physical fitness assessments or training sessions of the health programs. No other risks are expected.

Apart from that, the study participants will have to agree to the inclusion and exclusion criteria, undergo a detailed screening, and, in case of health problems or diseases, provide a medical certificate attesting their ability to participate in the trial and the health program. Moreover, the potential risks were reviewed by the Ethics Committee of the University of Freiburg and the principal medical investigator of the study.

Adverse and any other events will be documented in a standardized way at the medical examinations. The study participants will be asked to inform the study staff if any event occurs in the interim study phases. Adverse events will be reported to the principal medical investigator of the study and the entire project team. If any event occurs, the study participants will be able to cancel, interrupt, or repeat the medical examinations. They will also have the possibility to cancel, interrupt, or modify the health program. If necessary, immediate care and treatment measures will be initiated by the principal medical investigator. He will also be able to terminate participation prematurely if health problems occur that partially or entirely exclude participating in the trial and the health program. Travel accident insurance, including stays on-site, will be arranged for all study participants.

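### The diet diary follows the examination at t0 but precedes it at t1–t3, so pre-visit alcohol and fasting rules enter only the later diaries; the t1 tracker value is exposed to the exercise ban to an unstated degree

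*Protocol article*

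**What the plan says.** All of the following is in the protocol article.

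- **Diet diary (2.4.2 Secondary Outcomes):** "The nutritional protocols will be completed seven days after the first medical examination and seven days before the second, third, and fourth medical examination".
- **Activity tracker (2.4.2):** "Data will be collected daily between the first two measurement time points (t0–t1) and seven days after the follow-up measurement time points (t2, t3"). No section says which of the daily t0–t1 records form the t1 value.
- **Baseline for both behaviours (2.7 Recruitment):** "After a 7-day follow-up measurement of physical activity and dietary behavior, the baseline assessment and thus the study enrolment will be completed". Under 2.3.2, participants "will receive the respective health program after successful baseline assessment", so the week after t0 is still before the programme.
- **Visit preparation (2.4.2):** "The study participants will fast (meal and drinks, nicotine consumption: ≥12 h, alcohol consumption and exercise: ≥48 h"). It applies every time: "These criteria will be checked individually via an anamnesis at the beginning of each medical examination".
- **Use of the data:** Table 1 lists physical activity and dietary behaviour as secondary outcomes at all four time points. The Introduction states a hypothesis of improvement within each programme separately. Section 4.3 plans within-group comparisons of t0 with t1, t0 with t2, t1 with t2 and t2 with t3. No section excludes or adjusts for the days under restriction.

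**The concern.** The visit instructions suppress the behaviour being measured, and they fall inside some recording windows but not others. A diary that ends at the examination contains instructed alcohol abstinence and a fast. A diary that starts after the examination contains neither. The baseline diary is of the second kind and all later diaries are of the first, so part of any fall in recorded alcohol from t0 is produced by the schedule. That part points the same way as the hypothesis of improvement and recurs at t1, t2 and t3, so it could pass for a lasting effect. Randomisation does not protect a within-group change, because no other arm is subtracted.

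The tracker has a related mismatch. Its t1 value comes from before an examination and its other three values come from after one. Any exercise lost to the ban lowers t1 relative to t0 and then appears as a rise from t1 to t2.

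**Working it through.** The plan gives no figure to reproduce here. The check sets the windows against the restrictions.

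**Step 1. Side of the examination on which each value is recorded**

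| Outcome | t0 | t1 | t2 | t3 |
|---|---|---|---|---|
| Diet diary | after | before | before | before |
| Tracker | after | before (days not stated) | after | after |

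The restrictions apply only before an examination. They therefore touch the diary at t1, t2 and t3, and the tracker at t1 only.

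**Step 2. Which planned contrasts are unmatched**

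| Contrast | Diet | Tracker |
|---|---|---|
| t0 vs t1 | unmatched | unmatched |
| t0 vs t2 | unmatched | matched |
| t1 vs t2 | matched | unmatched |
| t2 vs t3 | matched | matched |

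**Step 3. Share of the window under restriction**

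- 48 h ban in a 7-day window before the examination: 2/7 = 28.6%. In a window after it: 0/7 = 0%.
- 12 h fast in the same window: 12/(7 × 24) = 12/168 = 7.1% of the hours. These hours lie within the 48 h.
- 48 h ban in all 12 weeks of tracker days: 2/(12 × 7) = 2/84 = 2.4%.

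**Step 4. Size for diet**

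Assumptions, not from the documents: mean alcohol intake 12 g/day, spread evenly over the week, nothing moved to other days, 7 kcal per g.

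- Apparent change from t0 with habits unchanged: 12 × 2/7 = 3.4 g/day lower. In energy: 12 × 2/7 × 7 = 24 kcal/day lower.
- At an assumed 5, 10 or 20 g/day, the apparent fall is 1.4, 2.9 or 5.7 g/day (intake × 2/7).
- If only 25% to 50% of the barred drinking is lost and the rest is moved within the week, the relative bias is 0.25 × 2/7 = 7% to 0.50 × 2/7 = 14%. At 12 g/day that is about 0.9 to 1.7 g/day.

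**Step 5. Size for activity**

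Input: 60 min/week, the upper limit for entry to the fitness trial (2.2 Eligibility Criteria). Assumptions: exercise spread evenly and not moved, no true change.

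- t1 value from the last 7 days: 60 × 5/7 = 42.9 min/week, an apparent change of −17.1. At t2 the value returns to 60, an apparent rise of 17.1.
- t1 value from all 84 days: 60 × 82/84 = 58.6 min/week, an apparent change of −1.4.

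**Step 6. Between groups**

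Both arms share the same windows. If each arm loses the same number of minutes, or grams, the loss cancels. If the loss is proportional to behaviour and nothing is moved, an assumed true t1 difference of 30 min/week is recorded as 30 × 5/7 = 21.4 with the last-7-days window, and as 30 × 82/84 = 29.3 with all 84 days.

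**The case against.** Several objections have force.

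- **The t1 tracker window is not fixed.** Data are daily, and the choice of days is a derivation rule that an analysis plan may settle. This stands: 29% is the upper end of a range that starts at 2.4%, and the restricted days can still be dropped. What does not depend on the choice is that every candidate day lies before the t1 examination.
- **Many contrasts are matched.** Step 2 bears this out. A reader might infer that all visit-to-visit changes in behaviour are distorted, and the text does not support that.
- **Arms are treated alike.** A reader might infer that the between-group difference at t1 is shrunk by 29%. That needs a proportional loss, no moving of exercise and the last-7-days window. The documents establish none of these. Moving is plausible, since examinations are scheduled in advance (4.1) and weekly plans in the interactive programme can be adapted (2.3.1).
- **The affected quantities are narrow.** The alcohol ban bears little on most nutrients, and the exercise ban bears more on exercise minutes than on steps or sedentary time. The timing of the IPAQ-L is not given, so nothing is shown for it.
- **The baseline placement has a reason.** Tracker and diary are introduced at the first examination, and the programme starts only after baseline. This explains the t0 window but does not remove the mismatch.
- **Soreness after the fitness tests.** One might argue that the post-visit weeks in the fitness trial are also depressed. Section 5.2 says only that "muscle soreness can occur in the following days after physical fitness assessments". It names a possibility, not an expected effect, so no size can be attached to it.

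**Conclusion.** The point holds, with limits. For diet it follows directly from the stated schedule: up to 2 of 7 days at t1–t3 and none at t0 are under visit restrictions, so within-group changes from t0 in alcohol, its energy and any score that counts alcohol lean towards apparent improvement. The size is about 3.4 g/day or 24 kcal/day under the assumed 12 g/day with nothing moved, and smaller otherwise.

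For activity, t0 vs t1 and t1 vs t2 are affected, mainly in exercise minutes. The restricted share is between 2.4% and 29%, depending on a t1 window that the article does not state.

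Diet t1 vs t2, activity t0 vs t2, and t2 vs t3 for both are matched on the side of the examination. Between-group bias is conditional on a proportional loss. The two primary outcomes, VO2max and body weight, are not affected. This is a modest and cheaply corrected flaw in secondary outcomes and does not threaten the trials' main conclusions.

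**What to change.** Add a derivation rule that applies equally in both arms:

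1. Leave the days under pre-examination restriction (the last two days and the fasting morning) out of the t1, t2 and t3 diary means.
2. State which days form the t1 tracker value and leave the restricted days out, for example by using the 7 days that end 48 h before the examination. Daily collection makes this possible without new data.

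The visit preparation rule itself need not change.

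**Cost.** Diary means rest on about 5 days instead of 7. If days are independent within a person, the day-to-day part of the standard error of one person's mean grows by a factor of √(7/5) = 1.18. The between-person part is unchanged, so the loss in the group comparison is smaller. The tracker value keeps its 7 days.

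Moving the t1 windows to after the examination would also put that visit on the same side as t0, but it is a trade-off: the week would fall outside the programme period and, in the fitness trial, would follow the fitness tests. The derivation rule avoids both.
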